## Withdrawal of Subjects from the Study

A volunteer is free to withdraw from the study at any time, for any reason without prejudice to any future medical care.

- - 1. Interruption of dosing

At visits 3, 6, 9, an assessment of the diary card, safety blood sample results, and visual inspection of the cervico-vaginal mucosa by a trained operator, will determine whether further immunisations will take place. Immunisations will be interrupted in the presence of any of the following:

1. Profuse, non-menstrual vaginal bleeding requiring transfusion, hospitalisation or bed rest for more than 24 hours for which there is no reasonable alternative explanation.
2. A grade 3 or 4 clinical or laboratory event confirmed on examination or repeat testing respectively and thought to be *probably related* to treatment
3. A grade 3 or 4 clinical or laboratory event confirmed on examination or repeat testing respectively and thought to be *possibly* related to gel, although in this case the investigator may choose not to interrupt treatment based on his clinical judgement.

Study treatment may be recommenced after interruption following an adverse event at the discretion of the clinical investigator. If the event recurs, and is grade 3 or 4, then treatment should be discontinued.

- - 1. Discontinuation of dosing

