## Allocation to treatment groups

Initially one subject will be recruited and allocated to receive 9 applications of 100µg of gp140 in 3.0 mL gel (total gp140 dose 0.9 mg) in an open-label, non-randomised manner.

Following satisfactory safety review at visit 6 (after three applications, see section 6.4.1) the remaining 29 subjects will be recruited as one cohort and will be allocated to one of the following dosing regimens/groups in a double‑blind, randomised manner:

Group 1: 19 subjects receiving 9 applications of 100µg of CN54gp140 in 3.0 mL gel intravaginally

Group 2: 10 subjects receiving 9 applications of 3.0 mL placebo gel intravaginally [CONTROL]

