#### The investigator may decide to discontinue dosing in a subject with interrupted dosing.

Immunisation must be discontinued in participants who are pregnant (confirmed positive pregnancy test). Every effort will be made to obtain documentary evidence of the outcome of pregnancy. Wherever possible, the subject will be followed up for adverse events and have safety bloods and monitoring if appropriate, but no immunogenicity samples will be obtained.

Participants who discontinue product either by choice or following advice from clinical personnel will be referred for a clinical examination, and for collection of all parameters listed at the final visit.

- - 1. Withdrawal

Withdrawal means discontinuation of study visits and immunisations, and the reasons for this should be recorded in the CRF. Examples for study withdrawal include:

- participant desire to stop participating in the trial
- investigator concerns that continuing visits is not in the best interest of the participant

A visual assessment of the cervico-vaginal mucosa will be made at visits 1, 2, 3, 6, 9, 12, 13, 14 15 and 16 and no immunisation or samples obtained if there is a break in the mucosal integrity.

Any comments (spontaneous or elicited) or complaints made by the subject and the reason for termination, date of stopping the study medication and the total amount of study medication must be recorded in the CRF and source documents.

Withdrawn subjects who have received any study medication are required (wherever possible) to undergo the final safety visit (Visit 15) procedures. Subjects who are withdrawn due to an AE will be followed-up until the event has stabilised.

The Chief Investigator will be notified within 24 hours of the decision to withdraw an individual subject.

- - 1. Policy for replacing withdrawals

If the first subject immunised withdraws or is withdrawn before safety evaluation on visit 6, or if they fail to receive three applications of study vaccine before visit 6, then they will be replaced, and another subject allocated to receive 9 applications of CN54gp140 in an open-label manner. Further replacements as necessary will be made until one subject has received three applications of study vaccine before visit 6.

There will be no further replacement of subjects withdrawn from the study in this hypothesis generating Phase I study once randomised, double-blind allocation to study groups 1 and 2 has commenced.

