The withdrawal of a subject from the study should be discussed where possible with the study monitor and reported to the Sponsor.

- 1. Criteria for Stopping Study

If the first subject recruited (or a replacement if withdrawal has occurred) has received three applications of study vaccine before visit 6, and has an unsatisfactory safety review on visit 6 as defined in section 6.4.1, such that dosing would be interrupted, then the study will be put on hold pending discussions with the main ethics committee and regulatory authority.

Several severe or serious AEs, which are probable in relation to vaccination will lead to the study being terminated at that point. The decision to stop the study rests on the Chief Investigator.

An unblinded Data Montioring Committee formed at St. George’s of experts who are not in any way involved with the safety assessment of trial subjects will review the accumulating immunogenicity results, and will advise the PIs on the value of continuing the trial. If a lack of significant immune response is observed, a decision will be made by the Chief Investigator, the Principal Investigators, and the Data Monitoring Committee regarding the premature termination of the trial.

The sponsor reserves the right to terminate the study at any time.

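### A waiver of dosing interruption under section 6.4.1 can leave the first-subject study hold in section 6.5 untriggered

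*Protocol*

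**What the plan says.** One subject is dosed first, open label. Section 5.1 makes recruitment of the other 29 conditional on her visit 6 review. It opens "Following satisfactory safety review at visit 6 (after three applications, see section 6.4.1" and gives no definition beyond that cross-reference.

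Section 6.5 sets the consequence of a bad review. If the first subject (or her replacement) has had three applications and has an "unsatisfactory safety review on visit 6 as defined in section 6.4.1, such that dosing would be interrupted", the study is held while the matter is discussed with the main ethics committee and the regulator.

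Section 6.4.1 begins "Immunisations will be interrupted in the presence of any of the following" and lists three items:

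- Item 1: "Profuse, non-menstrual vaginal bleeding requiring transfusion, hospitalisation or bed rest for more than 24 hours", with no reasonable alternative explanation.
- Item 2: a confirmed grade 3 or 4 clinical or laboratory event, probably related to treatment.
- Item 3: a confirmed grade 3 or 4 event, possibly related to gel, "although in this case the investigator may choose not to interrupt treatment based on his clinical judgement".

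The section does not use or define the terms satisfactory review or unsatisfactory review.

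**The concern.** Two decisions are tied together. Whether this woman may continue is a clinical judgement, and some discretion is reasonable. Whether the rest of the cohort may start without outside discussion is a study-level decision, and section 6.5 provides a hold for it. Because 6.5 borrows its trigger from the dosing rule, discretion given for the first decision appears to carry over to the second.

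This matters because the visit 6 review of one subject is the only pre-specified safety gate before the randomised cohort. With a single open-label subject and no comparator, possibly related is a realistic label for a first signal. Under section 8.2.3, probably related requires the vaccine to be the more likely cause. The same investigator assigns causality. Item 3 concerns events related to gel, and all 29 later subjects (19 on gp140 gel, 10 on placebo gel) receive gel.

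**Working it through.** The plan gives no figure to reproduce. The check is to set the provisions side by side.

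**Step 1: the trigger.** Section 6.5 can be read in two ways. (A) The hold applies whenever a listed 6.4.1 event is present; the reference to a definition in 6.4.1 and that section's opening words support this. (B) The hold applies only if her dosing would actually be interrupted; the closing clause of the 6.5 sentence supports this, and it is the more literal reading.

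| First subject at visit 6 | Her dosing under 6.4.1 | Hold under A | Hold under B |
| --- | --- | --- | --- |
| Item 1 event | interrupted, no waiver | yes | yes |
| Item 2 event | interrupted, no waiver | yes | yes |
| Item 3 event, not waived | interrupted | yes | yes |
| Item 3 event, waived | continues | yes | no |

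The readings differ in the last row only.

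**Step 2: does section 5.1 close the gap?** It adds a positive condition, a satisfactory review, and contains neither the interruption clause nor a hold. But it defines satisfactory only by sending the reader to 6.4.1, which has no definition. It does not say how a waived item 3 event counts.

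**Step 3: does another rule impose a hold?**

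- Termination in 6.5: "Several severe or serious AEs, which are probable in relation to vaccination will lead to the study being terminated at that point". One possibly related event does not meet it.
- Data Monitoring Committee (6.5, 7.5): reviews immunogenicity and is separate from safety assessment.
- Sponsor: "The sponsor reserves the right to terminate the study at any time". This is discretionary.
- Serious event and SUSAR reporting (8.2.3): covers serious events and imposes no hold. Section 8.2.3 itself notes that a severe event need not be serious.
- Mucosal break (6.4.3): "no immunisation or samples obtained if there is a break in the mucosal integrity". There is no waiver, so such a case falls outside the gap for as long as the break is present.

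**Step 4: what is left?** Mainly non-serious grade 3 events without a mucosal break. Examples in Appendix 1 (genital reactions) are oedema with intact epithelium, diffuse moderate or severe redness with grade 2 symptoms, and fresh non-menstrual bleeding for more than 4 days. Such bleeding escapes item 1 if it needs no transfusion, admission or bed rest beyond 24 hours.

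**Step 5: could such an event be seen by visit 6?** Nominal application days from visit 3 (day 0) to visit 6, from Tables 1 to 3:

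- Monday start: 0, 2, 4, 7
- Wednesday start: 0, 2, 5, 7
- Friday start: 0, 3, 5, 7

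Visit 6 is nominally 7 days after the first application and 2 to 3 days after the third. Bleeding that starts less than 7 − 4 = 3 days after the first application can therefore have passed 4 days by visit 6. These are nominal days; section 8.1 allows 2 days either side of each visit. After a waiver she could still receive 9 − 3 = 6 applications.

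**The case against.** The strongest reply is that the text is not truly ambiguous. Section 6.5 adds an operative test, interruption of dosing, and a waived event does not meet it. On that view the sponsor chose to let clinical judgement bear on events that, by the 8.2.3 definition, could have another cause, and the criticism is a preference. It stands that reading B is the more literal one. That does not dispose of the point: if B is intended, one dosing judgement decides whether a confirmed grade 3 or 4 event in the only sentinel subject triggers the hold. Section 6.4.1 already makes item 3 interrupt dosing, and so trigger the hold, by default.

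A second reply is that the gap is small. That stands. Each later subject also has her own reviews at visits 3, 6 and 9.

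Three stronger readings are tempting, and the documents do not support them:

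- That a waiver by itself opens recruitment of the 29. Section 5.1 still requires a satisfactory review, and a review could be called unsatisfactory with the waiver in place. The fault is that nothing says how to decide.
- That severe events could escape oversight altogether. Serious events go to the sponsor, and SUSARs to the ethics committee and regulators.
- That later subjects would be dosed at once, or after a definite interval. The screening timing in 8.1.1 is approximate, the schedule tables depend on cycle length, and it is not stated whether screening may start before visit 6. No interval is relied on here.

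**Conclusion.** The point holds in a narrow form. The hold in 6.5 depends on a definition that 6.4.1 does not contain and on an interruption that item 3 lets the investigator waive. On the more literal reading, a waived, confirmed grade 3 or 4 possibly related event in the first subject triggers no hold; 5.1 does not settle the matter, and no other rule imposes one.

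The gap covers 1 of the 3 items, only when waived, and mainly non-serious events without a mucosal break. How often such an event would occur or be waived cannot be computed from the protocol, so no risk figure is offered. The conclusion rests on the wording of 5.1, 6.4.1 and 6.5 and assumes that no other document defines the visit 6 review. Because this is the only pre-specified safety gate before randomised dosing, the trigger should be settled before the first application.

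**What to change.** In section 6.5, replace the clause that makes the hold depend on interruption. State that any confirmed item 1, 2 or 3 event of 6.4.1 in the first subject (or her replacement) at the visit 6 review makes that review unsatisfactory and puts the study on hold pending discussion with the main ethics committee and regulatory authority, whether or not her own dosing is interrupted. In section 5.1, cross-refer to this sentence where the satisfactory review is mentioned. Leave the item 3 waiver in 6.4.1 unchanged for individual dosing.

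The cost is one sentence and a cross-reference, with no added procedures, staff or subjects. The downside is a possible pause, of a length the protocol does not state, after one event of uncertain cause. If the sponsor intends the opposite rule, 6.5 should say explicitly that a waived item 3 event does not trigger the hold. That would remove the ambiguity but leave the weaker gate.

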#### The investigator may decide to discontinue dosing in a subject with interrupted dosing.

Immunisation must be discontinued in participants who are pregnant (confirmed positive pregnancy test). Every effort will be made to obtain documentary evidence of the outcome of pregnancy. Wherever possible, the subject will be followed up for adverse events and have safety bloods and monitoring if appropriate, but no immunogenicity samples will be obtained.

Participants who discontinue product either by choice or following advice from clinical personnel will be referred for a clinical examination, and for collection of all parameters listed at the final visit.

- - 1. Withdrawal

Withdrawal means discontinuation of study visits and immunisations, and the reasons for this should be recorded in the CRF. Examples for study withdrawal include:

- participant desire to stop participating in the trial
- investigator concerns that continuing visits is not in the best interest of the participant

A visual assessment of the cervico-vaginal mucosa will be made at visits 1, 2, 3, 6, 9, 12, 13, 14 15 and 16 and no immunisation or samples obtained if there is a break in the mucosal integrity.

Any comments (spontaneous or elicited) or complaints made by the subject and the reason for termination, date of stopping the study medication and the total amount of study medication must be recorded in the CRF and source documents.

Withdrawn subjects who have received any study medication are required (wherever possible) to undergo the final safety visit (Visit 15) procedures. Subjects who are withdrawn due to an AE will be followed-up until the event has stabilised.

The Chief Investigator will be notified within 24 hours of the decision to withdraw an individual subject.

- - 1. Policy for replacing withdrawals

If the first subject immunised withdraws or is withdrawn before safety evaluation on visit 6, or if they fail to receive three applications of study vaccine before visit 6, then they will be replaced, and another subject allocated to receive 9 applications of CN54gp140 in an open-label manner. Further replacements as necessary will be made until one subject has received three applications of study vaccine before visit 6.

There will be no further replacement of subjects withdrawn from the study in this hypothesis generating Phase I study once randomised, double-blind allocation to study groups 1 and 2 has commenced.

The withdrawal of a subject from the study should be discussed where possible with the study monitor and reported to the Sponsor.

- 1. Criteria for Stopping Study

If the first subject recruited (or a replacement if withdrawal has occurred) has received three applications of study vaccine before visit 6, and has an unsatisfactory safety review on visit 6 as defined in section 6.4.1, such that dosing would be interrupted, then the study will be put on hold pending discussions with the main ethics committee and regulatory authority.

Several severe or serious AEs, which are probable in relation to vaccination will lead to the study being terminated at that point. The decision to stop the study rests on the Chief Investigator.

An unblinded Data Montioring Committee formed at St. George’s of experts who are not in any way involved with the safety assessment of trial subjects will review the accumulating immunogenicity results, and will advise the PIs on the value of continuing the trial. If a lack of significant immune response is observed, a decision will be made by the Chief Investigator, the Principal Investigators, and the Data Monitoring Committee regarding the premature termination of the trial.

The sponsor reserves the right to terminate the study at any time.

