| Neuro-sensory | | Mild impairment (decreased sensation, e.g., vibratory, pinprick, hot/cold in great toes) in focal area or symmetrical distribution | | Mod impairment (mod decreased sensation, e.g., vibratory, pinprick, hot/cold to ankles) and/or joint position or mild impairment that is not symmetrical | | Severe impairment (decreased or loss of sensation to knees or wrists) or loss of sensation of at least mod degree in multiple different body sites (i.e., upper + lower extremities) | | Sensory loss involves limbs and trunk |
| Eye | |  | | Mild pain, visual changes, conjunctivae erythema, abnormal slit lamp | | Loss of vision, clinically diagnosed uveitis, mod-severe pain, glaucoma | | --------------- |
| Headache | | Mild, no Rx req, OR over the counter medication | Mod; OR requiring regular OTC or occasional prescription only medication | | | Severe; intractable; OR requiring repeated prescription only medication | | Requiring hospitalisation, or associated with neurological, respiratory or cardiovascular abnormalities |
| **MUSCULOSKELETAL** | | | | | | | | |
| Arthralgia/Arthritis | | Arthralgia | | Arthralgia with joint effusion or moderate impairment of activity | | Frank arthritis with or without effusion OR resulting in severe impairment of activity | | Hospitalisation |
| Myalgia | | Myalgia without limitation of activity | | Muscle tenderness at other than injection site or with moderate impairment of activity eg difficulty climbing stairs | | Frank myonecrosis OR with severe impairment of activity eg can’t climb stairs | | Hospitalisation |
| GENERAL | |  | |  | |  | |  |
| Fever  Oral>12 hours | 37.7 - 38.9°C  (100.0 – 101.5°F) | | 39.0 – 39.7°C  (101.6 – 102.9°F)  OR max temp of 103°F | | 39.8 – 40.5°C  (103 - 105°F)  OR max temp of 103.5°F | | >40.5°C (105°F)  OR max temp of >105°F | |

GENITAL REACTIONS

| PARAMETER | **Grade 1** | **Grade 2** | **Grade 3*** |
| --- | --- | --- | --- |
| **Mild** | **Moderate** | **Severe*** |
| **Symptoms and signs related to single application/acute genital toxicity/allergy** | Mild itching, soreness, slight redness | Moderate soreness and pain with vulval erythema and swelling | Some combination of frank erythema, pain, vulval oedema, rash/urticarial lesions spreading onto the abdomen/thighs, sloughing of mucosa |

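### A reaction that stops the first subject's dosing early leads to her replacement, not to the section 6.5 hold

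*Protocol*

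**What the plan says.** Section 5.1 has one subject treated open-label. The remaining 29 are recruited after a satisfactory safety review at visit 6, by which time she should have had three applications (visits 3, 4 and 5).

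Section 6.4.1 sets the criteria for interrupting dosing: profuse non-menstrual bleeding, or a confirmed grade 3 or 4 event that is probably or possibly related, with investigator discretion in the latter case. The formal reviews are placed as follows: "At visits 3, 6, 9, an assessment of the diary card, safety blood sample results, and visual inspection of the cervico-vaginal mucosa". Dosing can resume: "Study treatment may be recommenced after interruption following an adverse event at the discretion of the clinical investigator".

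Section 6.4.4 replaces the first subject if she withdraws or is withdrawn before the visit 6 evaluation, and also "if they fail to receive three applications of study vaccine before visit 6, then they will be replaced". It goes on: "Further replacements as necessary will be made until one subject has received three applications of study vaccine before visit 6". It makes no exception for a safety cause and sets no limit on the number of replacements.

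Section 6.5 puts the study on hold, pending discussion with the main ethics committee and the regulator, if the first subject or her replacement "has received three applications of study vaccine before visit 6, and has an unsatisfactory safety review on visit 6 as defined in section 6.4.1". The only other event-driven stop is: "Several severe or serious AEs, which are probable in relation to vaccination will lead to the study being terminated at that point". That decision rests with the Chief Investigator.

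**The concern.** The hold exists so that one qualifying event in the first woman dosed goes to the ethics committee and regulator before 29 more are exposed. As drafted, it depends on her having completed three applications. An event severe enough to stop dosing after one or two applications takes her outside the hold and into the replacement rule. The same event, if she completes three applications and it is found at visit 6, would require a hold. The rule is thus least responsive to the reactions that appear soonest and prevent further dosing.

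At stake is the exposure of a further woman, and then of the cohort, without the external review that the protocol otherwise requires.

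**Working it through.** **Rule logic.** There is no stated figure to reproduce, so the first step is to set the clauses beside each other for a first subject who meets a section 6.4.1 criterion.

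| Course | Three applications before visit 6? | Section 6.4.4 | Section 6.5 hold |
|---|---|---|---|
| Event found at visit 6, all three applications given | Yes | Not triggered | Triggered |
| Event after application 1 or 2, dosing interrupted but three applications still given, unsatisfactory at visit 6 | Yes | Not triggered | Triggered |
| Event after application 1 or 2, third application missed, attends visit 6 | No | Replace | Cannot be met |
| Event after application 1 or 2, leaves before visit 6 | No, or no visit 6 review | Replace | Cannot be met |

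In the last two rows her own event cannot produce the hold. The hold then passes to the replacement, and section 5.1 releases the 29 if the replacement passes.

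**Can those rows occur?** Bloods, mucosal examination and diary review are scheduled at visits 3 and 6 but not at visits 4 and 5 (Tables 1 to 3). Laboratory and mucosal findings after application 1 or 2 would therefore usually come to light at visit 6. However, section 8.2.3 has adverse events assessed at every visit and accepts spontaneous reports, so an overt reaction can stop dosing at visit 4 or 5. With applications on Mondays, Wednesdays and Fridays there is little time to restart. Appendix 1 has a row for "Symptoms and signs related to single application/acute genital toxicity/allergy", with grade 3 described as "Some combination of frank erythema, pain, vulval oedema, rash/urticarial lesions spreading onto the abdomen/thighs, sloughing of mucosa".

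**Size.** The protocol gives no rates, so the following are assumptions:

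- p: chance of a section 6.4.1 event per application, constant and independent; values 0.01, 0.02 and 0.05.
- q: share of women with an event after application 1 or 2 who are lost before visit 6 or miss the third application; values 0 to 1.
- Several events, in the termination rule, is read as two.

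For each subject in the first position:

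- early = 1 − (1 − p)²
- lost = q × early
- hold = (1 − q) × early + (1 − p)² × p
- pass = (1 − p)³

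Chance that the 29 are released after one unheld event = lost × pass. If the termination rule never applies, for example because events are only possibly related, it is lost × pass / (1 − lost).

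| p | early | pass | q = 0 | q = 0.25 | q = 0.5 | q = 1 | q = 1, no termination |
|---|---|---|---|---|---|---|---|
| 0.01 | 0.0199 | 0.9703 | 0 | 0.005 | 0.010 | 0.019 | 0.020 |
| 0.02 | 0.0396 | 0.9412 | 0 | 0.009 | 0.019 | 0.037 | 0.039 |
| 0.05 | 0.0975 | 0.8574 | 0 | 0.021 | 0.042 | 0.084 | 0.093 |

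Example, p = 0.05 and q = 0.5: lost = 0.5 × 0.0975 = 0.04875, and 0.04875 × 0.8574 = 0.042.

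**Chance of a hold, as written and amended.** As written: hold × (1 + lost), counting at most one replacement. If every section 6.4.1 event after applications 1 to 3 triggers the hold: 1 − (1 − p)³. At q = 0.5:

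- p = 0.01: hold = 0.00995 + 0.9801 × 0.01 = 0.01975. As written 0.01975 × 1.00995 = 0.020; amended 0.030.
- p = 0.05: hold = 0.04875 + 0.9025 × 0.05 = 0.09388. As written 0.09388 × 1.04875 = 0.098; amended 0.143.

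**The case against.** The route needs a chain of conditions in one woman: a qualifying event after application 1 or 2; confirmation of a grade 3 or 4 event although visits 4 and 5 schedule no examination or bloods; loss of the third application or of visit 6; no timely restart; no discretionary action; and a replacement who passes. This stands. It makes q well below 1 likely, and the q = 1 column is an upper bound.

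Other safeguards exist. The Chief Investigator is told within 24 hours of a withdrawal decision (section 6.4.3), withdrawals are reported to the sponsor, and the sponsor may terminate at any time (section 6.5). The definition of a serious event is broad. Section 8.2.3 treats any related event as unexpected, so a serious one would be reported to the ethics committee and regulators as a SUSAR. Section 6.4.4 sets no timing and does not forbid a pause before a replacement is dosed. All this is correct, and it reduces the uncovered case mainly to a single non-serious grade 3 event. None of it requires a hold: each safeguard is a notice, a discretion, or a rule needing more than one event.

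The Appendix 1 scale is generic and contains rows irrelevant to this trial. The genital row therefore shows that such a reaction can be graded, not that it is expected. The hold also stays live for the replacement, so what is lost is the hold for the first woman's event.

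Finally, p, q and the reading of several as two come from outside the protocol. The probabilities illustrate the size of the gap; the textual point does not depend on them.

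**Conclusion.** The point holds. Read together, sections 6.4.4 and 6.5 mean that a section 6.4.1 event that prevents the third application, or removes the first subject before visit 6, leads to replacement and cannot trigger the hold. This follows from the text without any assumption.

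The practical size is small and uncertain: nil at q = 0; about 0.5% to 2.1% at q = 0.25 and 1.0% to 4.2% at q = 0.5, for p from 0.01 to 0.05. The extreme in the range examined is 9.3%, at p = 0.05 with every early reactor lost and the termination rule never applying. No endpoint or analysis is affected, and the woman remains in the safety population if she has follow-up data. It should still be corrected, because it weakens the one mandatory safety gate before 29 women are randomised and the correction is cheap.

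**What to change.** In section 6.5, apply the existing hold to any section 6.4.1 event for which dosing was, or would be, interrupted, occurring after any of applications 1 to 3 in the first subject or a replacement, whether or not three applications were given. In section 6.4.4, allow replacement without a hold only when the loss did not involve such an event.

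The section 6.4.1 criteria stay as they are, including the investigator's discretion for possibly related events. Women who withdraw for milder reactions or other reasons are replaced as now.

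The cost is a protocol amendment of one or two sentences, with no added visits, samples or subjects. The price is a somewhat higher chance of a temporary hold: at q = 0.5, a rise of about 1 percentage point at p = 0.01 and about 4.4 points at p = 0.05 (0.1426 − 0.0985). These are the cases the hold was meant to cover.
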